## Methods/design

### Study design

This is a multicenter, open-label, randomized controlled clinical trial with two parallel arms, combined epidural-general anesthesia plus postoperative epidural analgesia group (EGA group) and general anesthesia plus postoperative intravenous analgesia group (GA group). A total of 1800 patients undergoing major thoracic and abdominal surgery will be recruited, with 900 patients for each group. The study is coordinated by the Department of Anesthesiology and Critical Care Medicine of Peking University First Hospital, and Peking University Clinical Research Institute is responsible for the study monitoring, data management and data analysis. Other centers participating in the study include Peking University People’s Hospital, Peking University Third Hospital, Beijing Hospital, and Beijing Shijitan Hospital, all of which are teaching hospitals of Peking University.

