### Randomization

The randomization will be performed centrally at Peking University Clinical Research Institute through an interactive web response system (IWRS, Brightech Clinical Information Management System) on the day of surgery just before anesthesia. The randomization is stratified by medical center and type of surgery (thoracic or abdominal surgery) (Fig. 1).

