### Data analysis

All statistical analyses will be performed with SAS statistical package, version 9.3 (SAS Institute, Cary, NC, USA) by statisticians at Peking University Clinical Research Institute. Analyses will be done on an intention-to-treat basis, that all subjects will be analyzed in the group which they were assigned to.

Primary outcome (the 7-day incidence of postoperative delirium) will be analyzed using Cochran-Mantel-Haensel Chi-squared tests, stratified by medical center and type of surgery (thoracic or abdominal surgery). The 95 % confidence interval of the incidence of each group and the difference between the two groups will be calculated. Logistic regression will be used for further analysis if an adequate number of events are observed or any impact or relative factor is expected according to the results of single-factor analysis. For the secondary outcomes, continuous variables (the dose of medications, the NRS pain scores after surgery) will be analyzed using an unpaired T-test, Mann–Whitney U test or repeated-measure analysis of variance; categorical variables (the incidences of non-delirium complications, the daily prevalence of delirium, and the 30-day mortality rate) will be analyzed using the Chi-squared test, continuity correction Chi-squared test or Fisher exact test; time-to-event results (time to onset of delirium or non-delirium complications, duration of hospitalization after surgery) will be analyzed using the Kaplan-Meier estimator, and the differences between groups will be tested by the log-rank test. Also the Cox proportional hazards model will be used to estimate the overall survival HR and 95 % confidence interval.

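### The tests named for the secondary outcomes ignore the randomisation strata, so they can lose some power where centre or surgery type predicts the outcome

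*Protocol article*

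**What the plan says.** The Randomization section of the protocol article states: "The randomization is stratified by medical center and type of surgery". Study design names a coordinating hospital and four other centres, so there are five centres and up to 5 × 2 = 10 strata.

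The Data analysis section carries both factors into the primary outcome, 7-day delirium, which is tested with "Cochran-Mantel-Haensel Chi-squared tests, stratified by medical center and type of surgery (thoracic or abdominal surgery". For the secondary outcomes it names the following:

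- Continuous (medication dose, pain scores): "will be analyzed using an unpaired T-test, Mann–Whitney U test or repeated-measure analysis of variance".
- Categorical (non-delirium complications, daily delirium prevalence, 30-day mortality): "will be analyzed using the Chi-squared test, continuity correction Chi-squared test or Fisher exact test".
- Time to event (onset of delirium or complications, hospital stay): Kaplan-Meier curves, where "the differences between groups will be tested by the log-rank test".

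No stratum or covariate is attached to any of these. A Cox model is named for the survival hazard ratio, with strata and covariates unstated. Logistic regression appears only as conditional further analysis, among the sentences on the primary outcome.

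**The concern.** Stratified randomisation with balance inside each stratum removes chance differences in stratum mix between the arms. The between-arm difference then varies less from trial to trial than under simple randomisation. A test that ignores the strata still counts the between-stratum variance in its standard error. If the strata predict the outcome, that standard error is too large, the p-value is too large on average, and a real effect is harder to detect.

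Centre and surgery type could plausibly matter here. The anaesthesia sections leave the maintenance technique open and additional opioids to judgement, and the Discussion says that centres and procedures are meant to vary. Pain scores, drug doses, hospital stay and common complications are the outcomes most exposed. What is at stake is precision on secondary outcomes, not the validity of the trial.

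**Working it through.** The plan gives no figure on this point; its sample size concerns the primary outcome only. What follows is a sensitivity calculation.

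**Inputs from the protocol article.** 1800 patients, 900 per arm (Study design); up to 10 strata; two-sided 5% level (Sample size estimation).

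**Inputs assumed.** R², the share of outcome variance explained by the strata; exact 1:1 balance within strata; and, for binary outcomes, stratum sizes, event rates and treatment effects. The article gives none of these, and no block scheme.

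**Continuous outcomes, normal theory.** Under balance the unstratified Z statistic has null variance 1 − R². Put s = √(1 − R²).

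- Overstatement of the standard error: 1/s − 1.
- Real type I error: 2 × [1 − Φ(1.96/s)].
- Power where a stratified test has 80%: 1 − Φ(1.96/s − 2.80), with 2.80 = 1.96 + 0.84.

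For R² = 0.10, s = 0.949 and 1.96/s = 2.066. The type I error is 2 × [1 − Φ(2.066)] = 3.9%, and the power is Φ(2.80 − 2.066) = 76.9%.

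| R² | SE overstated by | Real type I error | Power instead of 80% |
|---|---|---|---|
| 0 | 0% | 5.0% | 80.0% |
| 0.05 | 2.6% | 4.4% | 78.5% |
| 0.10 | 5.4% | 3.9% | 76.9% |
| 0.20 | 11.8% | 2.8% | 72.9% |

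**Binary outcomes, simulation.** 1800 patients in 10 balanced strata, 20,000 runs per scenario. Assumed centre shares are 40, 20, 15, 15 and 10%, with a quarter of surgery thoracic. Moderate differences mean thoracic risk × 2 and centre multipliers 0.6 to 1.6. Extreme differences mean × 3 and 0.3 to 2.5. Assumed relative risks under treatment are 0.4, 0.7 and 0.8 at event rates of 1%, 15% and 30%.

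| Event rate | Pearson type I error, moderate | Power lost against CMH, moderate | Pearson type I error, extreme | Power lost, extreme |
|---|---|---|---|---|
| 1% | 5.0% | 0.1 points | 4.7% | 0.6 points |
| 15% | 4.6% | 0.9 points | 2.8% | 4.1 points |
| 30% | 3.8% | 2.5 points | 2.0% | 7.6 points |

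With no stratum differences the Pearson test ran at 4.9 to 5.3%. CMH ran at 4.8 to 5.3% in every scenario. At a 1% event rate the strata can explain little variance (R² about 0.003 moderate, 0.012 extreme), which is why mortality, if rare, is hardly touched.

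The continuity-corrected test is more conservative still, but largely for a different reason: at a 1% rate with no stratum differences it already ran at 2.6%.

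The log-rank and rank tests were not simulated. The same mechanism applies, and the first table is only a guide to its size.

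**The case against.** **The article is condensed, and a statistical analysis plan could stratify these tests.** This stands in part. The article is not silent on the secondary tests: it names them, and the same paragraph says so where stratification is meant. A later plan that stratified would have to depart from the t-test, Mann-Whitney, chi-squared and Fisher tests named. The log-rank wording is less firm, because a log-rank test can be stratified without changing its name.

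**The intervals.** A reader might infer that the primary confidence interval is unstratified and conflicts with the CMH test. The documents do not support that. The article says only that the "confidence interval of the incidence of each group and the difference between the two groups will be calculated", without giving the method. The only secondary interval named is for the Cox hazard ratio, whose strata are also unstated. Silence on interval method in an article is not an error.

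**The conservatism is conditional.** This stands. A reader might take the secondary p-values to be too conservative as a matter of fact. That needs strata that predict the outcome and balance within them, and the article reports neither.

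**The size of the loss.** A reader might equate the sample-size loss with R², giving 10% and 20% at R² = 0.10 and 0.20. Under balance that is too much, because only the critical value is inflated. At 80% power the loss is 1 − [2.80/(1.96/s + 0.84)]². That is 1 − (2.80/2.91)² ≈ 7% at R² = 0.10, and 1 − (2.80/3.03)² ≈ 15% at R² = 0.20.

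**Little is at stake.** This also stands. The error is in the safe direction, the primary test already follows the design, and using different methods for primary and secondary outcomes is not wrong in itself. For sparse outcomes Fisher's exact test is defensible.

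**Conclusion.** The point holds as one of efficiency. The design stratifies on two factors, the primary test uses them, and the tests named for the secondary outcomes do not. Where the strata explain 5 to 20% of outcome variance and the arms are balanced within them, the secondary tests run at about 4.4 to 2.8% instead of 5%, and 80% power falls to between 78.5% and 73%. If the strata explain nothing, nothing is lost.

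For binary outcomes with moderate stratum differences the loss is at most about 2.5 power points at the rates examined, and practically nil for mortality if it is rare. Losses of 4 to 8 points need extreme differences. All these sizes rest on assumed R², stratum sizes and stratum rates.

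Type I error is not inflated and the primary test is not affected. The change is worth making because it costs almost nothing, but it corrects no fault of validity.

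**What to change.** State in the Data analysis section, or in the statistical analysis plan before the data are examined by group, that secondary comparisons use the randomisation strata:

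- Common binary outcomes: CMH test by centre and surgery type.
- Time-to-event outcomes: stratified log-rank test and stratified Cox model.
- Pain and dose: linear, rank-based or repeated-measures models with centre and surgery type as terms.
- Sparse outcomes: keep an exact test, or pool small strata by a rule fixed in advance. At an assumed 1% mortality, 1800 × 0.01 = 18 deaths would fall across up to 10 strata, fewer than two each on average.

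As a clarification rather than a correction, name a Mantel-Haenszel risk difference for the primary confidence interval, so that it matches the CMH test.

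The cost is wording and slightly more programming. The strata are already recorded for randomisation and needed for the primary test. The Trial status section reports that recruitment is continuing, so the choice can still be fixed ahead of the analysis.

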## Discussion

This multicenter, open-label, randomized, parallel-controlled clinical trial is designed to test the hypothesis that, compared with general anesthesia plus postoperative intravenous analgesia, combined epidural-general anesthesia plus postoperative epidural analgesia reduces the incidence of delirium in elderly patients during the first seven days after major thoracic and abdominal surgery.

Epidural anesthesia and analgesia is widely used for patients undergoing major surgery in combination with general anesthesia. In a large population-based retrospective cohort study of 259037 patients who underwent intermediate-to-high risk non-cardiac surgery between 1994 and 2004, 22 % received epidural anesthesia [58]. In another population-based historical cohort study of 29743 patients who underwent elective major surgery between 2004 and 2011, 27 % received combined general and neuraxial anesthesia [59]. Previous studies showed that, when compared with general anesthesia and opioid analgesia, epidural anesthesia and analgesia decreases the risk of pneumonia, improves the recovery of gastrointestinal function, and reduces the 0-to-30-day mortality after major surgery [28, 33, 60, 61]. However, the impact of the type of anesthesia on the incidence of postoperative delirium was only compared between regional and general anesthesia [40–42].

In the present study, a multicenter design is adopted so that patients enrolled in the study include a variety of surgical procedures under different clinical environments. This will increase the generalizability of our results. Because of the apparent difference between the two anesthesia-analgesia methods, a double-blind design cannot be achieved. Therefore, we had to use an open-label design. The following measures will be undertaken to decrease the risk of potential bias. Firstly, we use central randomization. Secondly, we require that all study personnel who are in charge of postoperative delirium assessment are not involved in intraoperative anesthesia and postoperative management of the enrolled patients, and thus they have no interest conflicts with the results of the study. Thirdly, all study personnel are trained to follow a standard procedure for the preoperative visit and postoperative follow-up and assessment.

Both the Confusion Assessment Method (CAM) [62, 63] and the CAM-ICU [43, 44] can be used for delirium assessment with sufficient sensitivity and specificity and have validated Chinese versions [64, 65]. The former is suitable for non-intubated patients, the later can be used for both intubated and non-intubated patients. In the present study, although the majority of our patients will not be admitted to the ICU with endotracheal intubation, we chose to use the CAM-ICU because of the following reasons. Firstly, the level of sedation/agitation will be assessed and the subtype of delirium (hypoactive, hyperactive, or mixed) can be classified with the use of CAM-ICU [47, 48]. Secondly, the use of a same assessment method for patients with and without endotracheal intubation may be helpful to avoid the potential bias. Thirdly, our team members are more familiar with the CAM-ICU because of previous studies [4, 57].

Strengths of the protocol include that it is the first multicenter, large sample size and centrally randomized study and that it observes both the primary (the 7-day incidence of postoperative delirium) and secondary endpoints (duration of postoperative delirium, incidences of non-delirium complications, length of stay in hospital after surgery, all-cause 30-day mortality, etc.). Results of the study will provide evidence for chosing appropriate method of anesthesia and analgesia in elderly patients undergoing major thoracic and abdominal surgery.

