#### Primary outcome

The primary outcome is the 7-day incidence of postoperative delirium. Patients will be assessed for delirium with the CAM-ICU twice daily (from 8 to 10 a.m. and from 6 to 8 p.m.) during the first seven days after surgery. Study personnel who assess delirium do not participate in intraoperative anesthesia and postoperative management of patients.

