#### Secondary outcomes

Secondary outcomes include the duration of postoperative delirium, the intensity of pain during the first three days after surgery, the occurrence of non-delirium complications within 30 days after surgery, the length of stay in hospital after surgery, and the 30-day all-cause mortality.

The intensity of postoperative pain both at rest and with coughing will be evaluated twice daily at the same time of delirium assessment (i.e., from 8 to 10 a.m. and from 6 to 8 p.m.) with the numeric rating scale (NRS, a 11-point scale where 0 indicates no pain and 10 indicates the worst pain). For patients who are deeply sedated or unarousable (−4 or −5 on the RASS), pain evaluation will be stopped temporarily and repeated later. Analgesic consumption will be recorded daily during the first three days after surgery. Non-delirium complications are defined as medical conditions other than delirium that required therapeutic intervention.

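### Delirium assessors are kept out of patient care but not masked to allocation, because the protocol goes straight from no double-blinding to open-label for a rater-judged primary outcome

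*Protocol article*

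**What the plan says.** The Study design section labels the trial open-label: "This is a multicenter, open-label, randomized controlled clinical trial with two parallel arms". The Discussion gives the visible difference between the two methods as the reason and concludes that "a double-blind design cannot be achieved. Therefore, we had to use an open-label design".

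The Discussion lists three measures against bias: central randomization, delirium assessors who take no part in care, and standardized training. The Primary outcome section states the second of these as "Study personnel who assess delirium do not participate in intraoperative anesthesia and postoperative management of patients". The Discussion justifies it by saying that "thus they have no interest conflicts with the results of the study". Masking of assessors to allocation is neither listed among the measures nor discussed as an option.

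Under Personnel training and delirium assessment, delirium requires a RASS score of −3 or above, CAM-ICU features (a) and (b), and either (c) or (d). These features include inattention and disorganized thinking. Assessment is twice daily for seven days. The Secondary outcomes section says that pain "will be evaluated twice daily at the same time of delirium assessment". After surgery one arm has a patient-controlled epidural pump and the other an intravenous one.

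**The concern.** A double-blind design and an open-label design are not the only two choices. An assessor-masked design needs only that the person rating the outcome does not know the arm. The hardest requirement, a separate group of assessors, is already met here.

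Being outside the care team removes one motive for bias, a stake in how one's own patients fare. It does not remove expectation. The stated hypothesis is directional (less delirium with EGA), and a rater who knows the arm may resolve borderline CAM-ICU features accordingly. The other two measures do not close the gap: central randomization protects allocation before assignment, and training standardizes technique.

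Any such shift enters the primary comparison directly. The planned analysis stratifies by center and type of surgery. It compares recorded cases and cannot tell a true difference from one created by differential recording.

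**Working it through.** **Logic.** The premise in the Discussion concerns double-blinding only, and its ground is that the two methods visibly differ. The conclusion is open-label. The intermediate option, masked assessors with unmasked patients and clinicians, is not considered. The safeguard that is stated concerns involvement in care and conflict of interest, not knowledge of the arm.

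**Size: a hypothetical illustration.** No figure in the plan depends on masking, so there is none to reproduce. No misclassification rate is given, so the fractions below are assumptions.

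Inputs:
- GA incidence 13.1% (Sample size estimation), taken as the true rate in both arms, so that there is no real effect.
- n = 832 per arm, as stated there before dropout. Whether 832 follows from its own inputs is a separate question.
- Two-sided significance level 0.05, critical value 1.96.
- f = assumed fraction of EGA patients with delirium who are recorded as not having it. GA is recorded without error.

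Formulas:
- Recorded rates: p_GA = 0.131 and p_EGA = 0.131 × (1 − f); d = p_GA − p_EGA; p̄ = their mean.
- SE0 = √[2 p̄(1 − p̄)/n]
- SE1 = √[(p_GA(1 − p_GA) + p_EGA(1 − p_EGA))/n]
- Chance of a significant result favouring EGA = Φ[(d − 1.96 × SE0)/SE1]

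| f | p_EGA | d | SE0 | SE1 | (d − 1.96 SE0)/SE1 | Chance of false result favouring EGA |
|---|---|---|---|---|---|---|
| 0 | 0.1310 | 0 | – | – | −1.96 | 2.5% |
| 10% | 0.1179 | 0.0131 | 0.01618 | 0.01618 | −1.15 | about 12% |
| 15% | 0.1114 | 0.0197 | 0.01600 | 0.01599 | −0.73 | about 23% |
| 20% | 0.1048 | 0.0262 | 0.01581 | 0.01580 | −0.30 | about 38% |

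Counting rejections in either direction, the rates for f = 10%, 15% and 20% are 12.8%, 23.3% and 38.1%. With 900 per arm they are 13.4%, 24.8% and 40.7%, so the choice between 832 and 900 matters little.

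**Scale against the target.** A 30% reduction from 13.1% gives 9.17%, a planned difference of 3.93 points. The spurious differences above are 1.31, 1.97 and 2.62 points, that is one third, one half and two thirds of it.

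**The other direction of error.** If 1%, 2% or 3% of GA patients without delirium were recorded as cases and EGA were recorded correctly, the GA rate would become 13.97%, 14.84% or 15.71% (0.131 + 0.869 × the fraction). The two-sided rejection rate would then be about 8%, 18% or 33%.

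**The case against.** **The protocol is open about its design and limits rater discretion.** It discloses the open-label design. A psychiatrist trains the assessors in a two-step procedure with an explicit diagnostic rule, and one instrument is used for all patients, partly to avoid bias. This stands as mitigation. It narrows the room for judgement but does not replace masking.

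**The figures are assumed and one-directional.** This also stands. There are about 14 assessments per patient (2 × 7). An EGA patient is lost as a case only if every positive assessment is miscalled, so a given per-visit bias shrinks at patient level except in brief or borderline episodes. Over-calling in GA works the other way, since one false positive makes a case and the chance accumulates over visits. The fractions used above apply to patients, not visits, and say nothing about how much bias to expect.

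**A condensed article leaves out operational detail.** Pump covers or access to records could well sit in the full protocol. But on the design itself the article is not silent: it states the open-label choice, argues for it and lists its safeguards without masking.

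**Stronger readings that the text does not support.** A reader might infer that the protocol declares all blinding impossible because anaesthetists cannot be blinded. It does not: it cites the visible difference between the methods, does not name anaesthetists in that argument, and rules out only double-blinding. A reader might also take it as stated that assessors know the hypothesis, see the pump and catheter, or score pain themselves. The first two are plausible inferences. On the third, the text fixes only the timing of the pain score, not who takes it.

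**Masking would be imperfect and burdensome.** Covering pump and dressing at every visit could mean up to 1800 × 14 = 25,200 visits, and patients may reveal their arm. That argues against requiring covers throughout, not against withholding allocation information.

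**Conclusion.** The point holds in a limited form. The article infers open-label from the impossibility of double-blinding, relies on the assessors' independence from care, and does not provide for masking them, although separate assessors already exist and the primary outcome needs judgement. Ascertainment bias is therefore possible, and the planned analysis cannot remove it. The documents contain no evidence that such bias occurs.

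The increase from 2.5% to about 12%, 23% or 38% rests on three assumptions: no true effect, an incidence of 13.1% with 832 per arm, and patient-level under-calling of 10%, 15% or 20% confined to EGA. It shows that modest differential error would be enough to mislead. It does not estimate the error, and the case for the change rests on the design argument. The change should be made. Its absence does not by itself invalidate the trial.

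**What to change.** In the Primary outcome section and the Discussion, state that delirium assessors are masked to allocation as far as feasible, and say how:

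- They have no access to the IWRS result, the anaesthesia record or the analgesia orders.
- CAM-ICU is completed before the pain score at each visit.
- Pump readings and analgesic consumption are not collected by the delirium assessor.
- Pump and line are kept out of view where practical, without requiring ward staff to cover them at every visit.
- The assessor's guess of the arm is recorded once, and its agreement with the actual arm is reported.

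The Discussion should also say that only double-blinding is unachievable and acknowledge that assessor masking will be partial.

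Cost: a short procedural text, one CRF item and a small burden at visits. The assessors are already separate from care, so withholding information, reordering the forms and recording the guess need no extra staff. The Trial status section says that recruitment is under way, so the change needs a modification approved by the IRB, as the Ethics approval section provides, and can cover only the remaining patients. Record the date of the change, so that results before and after it can be told apart.
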